### Recruitment

The enrollment of patients will be performed mainly from our Clinical Service at the School of Psychology, and by referral from Primary Care Physicians. After initial referral, potential patients with first episode MDD as primary diagnosis, will undergo the general inclusion and exclusion criteria check list in order to assess their potential eligibility.

We will also use social media (such as the Lab Facebook page), as well as flyers posted in specific spaces such as clinical settings (hospital, clinics), Universities, etc. The first screening will be performed by a research assistant (with a clinical Psychology degree) and the full assessment of the patient will be done by a clinician specialized in MDD (blinded to the study arm).

### Randomization

Once eligibility and consent have been approved and obtained, randomization will occur using the randomized list generated by an automatic web-based randomization program. Patients will be randomly assigned to one of the two groups in a 1:1 allocation ratio. Randomization order will be kept in sealed envelopes; therefore, patients will get their assignment according to the order of entrance in the study. This will also ensure that all patients and all other investigators are kept blind to this assignment for the duration of the study (allocation concealment) (see Figure 1, for study overview).

The randomization procedures described above will be followed for assignment to treatment groups. Following initial screening, during participant enrollment, a research associate will assign them to their randomly generated treatment group, keeping all patients and all other investigators blind to this assignment for the duration of the study.

### Blinding Procedure and Assessment

Participants, the psychologists performing the CBT, the ones performing the assessments, as well the statistician will remain blinded to the tDCS condition up to the end of the clinical trial, ensuring a triple blind design. Researchers applying tDCS will not be blinded. If a serious adverse event occurs, the Principal Investigator (PI) will be responsible for removing the blinding and notify the Ethics Committee within 24 h.

Blinding assessment will be performed to both participants and researchers who assessed the outcomes.

### Assessments

#### Eligibility and tDCS Assessments

*Questionnaire to assess eligibility to participate in the study*: this questionnaire aims to evaluate inclusion and exclusion criteria to participate in the study. It includes specific questions about neurologic and psychiatric history, history of head injuries, drugs use, and/or abuse, history of treatments, etc.

*Side Effects Questionnaire*: At each stimulation session, patients will complete a questionnaire to evaluate potential adverse effects of tDCS (tingling, burning sensation, headache, neck pain, mood alterations). If any side effects are reported, the degree of relatedness to the intervention will be assessed on a 5-point scale. This type of adverse events questionnaire has been used frequently in our previous tDCS studies (46–52) including in patients with MDD. In order to further control for changes in suicidal thoughts, we will add a specific question for suicide that can be follow-up with the SSI, if scores are equal to or >3.

*The Structured Clinical Interview for DSM 5 (SCID 5):* this is a semi-structured clinical interview (the clinician version) that guides the clinician step-by-step through the DSM-5 diagnosis process. This interview will be essential to confirm the diagnosis of first episode MDD and to evaluate for possible comorbid psychiatric disorders (43).

*Scale for suicide ideation (SSI):* this is a 19-item scale that aims to quantify and assess suicidal intention (42). Patients scoring SSI≥6 will not be enrolled in the study (53).

*tDCS blinding questionnaire*: After the treatment has ended, patients will complete a questionnaire to determine if our blinding methods were effective. We are using a 30 s sham montage, just as we use in our other trials, keeping the device on the subject for the duration of the session. The tDCS blinding questionnaire is organized in two main questions: 1. Please answer the questions to the best of your ability: 1.1 Did you receive: Sham Stimulation (tDCS) or Active Stimulation (tDCS); 1.2 Please, rate how confident you feel in your answer (please check one), from 1 (not confident at all), 2, 3 (somewhat confident), 4, to 5 (completely confident).

#### Demographic and Clinical Assessments

*Demographics information:* We will record information about the demographic characteristics of the study population such as age, gender, race, level of education, and social status.

*Medication Use Log:* Medication use information will be obtained at enrollment and updated on a weekly basis, by means of a Medication Log. Participants will record their current medications and dosages weekly, until completion of the study. Medication diaries are commonly used to record changes in medication use during the study period. We will also use the Antidepressant History Treatment Form (ATHF) to assess treatment refractoriness.

*Montgomery-Asberg Depression Scale* (MADRS): For the depression improvement assessments, we will use the MADRS for the primary outcome. This is widely used scale for the measurement of severity of depressive symptoms in patients with MDD. The scale is divided into 10 items, each scored on a 0 to 6-point ordinal scale (54). The MADRS will be administered according to a structured interview procedure that has been empirically found to result in high inter-rater reliability scores.

*Beck Depression Inventory (BDI):* This self-report inventory consists of 21 multiple-choice questions and is a widely used method to classify depression severity (55). It assesses for the presence of several symptoms related to depression, such as irritability, hopelessness and decreased cognitive performance. Physical symptoms such as weight loss and fatigue are also included. The total time required to complete this inventory is 5 to 10 min.

*Quality of Life Assessment (Short version of SF-36):* The short version of the SF-36 health survey is used as a measurement of quality of life. It provides a profile of functional health and well-being scores. It is also used as a psychometrical index of physical and mental health (56).

*Satisfaction with Life (SWL)*—is a short and rapid 7-point Likert scale that measures life satisfaction in the perspective of subjective well-being. Scores in SWL have been positively correlated with measures of mental health and also predictive of future maladaptive behaviors such as suicide attempts (57, 58).

*The Pittsburgh Sleep Quality Index (PSQI)*: a 19-item, self-report measure to evaluate overall sleep quality, primarily designed to evaluate sleep disturbance in patients with psychiatric disorders. The PSQI evaluates sleep quality in 7 categories: subjective sleep quality, sleep latency, sleep duration, habitual sleep efficiency, sleep disturbances, use of sleep medication, and daytime sleep dysfunction (59, 60).

*State-Trait Anxiety Inventory (STAI-Y) –* a self-report measure is organized in two subscales: State Anxiety Scale (S-Anxiety) wish measures the current (“right now”) presence and severity (state) of anxiety; and the Trait Anxiety Scale (T-Anxiety) which measures the general propensity to be anxious (trait). This measures focus on several domains that characterizes anxiety, such as subjective feelings, and levels of arousal (activations of the autonomic nervous systems). The trait subscale evaluates the more stable aspects of anxiety (“anxiety proneness”), such for instance worry, confidence and security (61).

*Beck Anxiety Inventory (BAI):* is a 21-item measure of anxiety focusing on somatic symptoms of anxiety. Each item is descriptive of somatic, subjective or panic-related symptoms of anxiety. Administration of BAI takes between 5 to 10 min. Since BAI focus on a “pure” measure of anxiety such as nervousness, dizziness, inability to relax, etc.), it helps discriminating between depression and anxiety (62, 63).

#### Data Management and Access to Data

Data forms and questionnaires will be coded in a standardized manner, and double-entered in a protected excel sheet. Personal information and all data collect will be kept in locked cabinets that only the principal investigator will have access. A key to access these cabinets will be kept in a safe place with limited access. Only researchers involved in the study and any public health and safety authorities will have access to the data collected in the study. Any information linking data back to the participant will be discarded to ensure that the data are truly anonymous. Data destruction will be conducted 5 years after the study has ended. Data sharing will only be possible after an agreement. The data will be stored and managed following the GDPR in the EU. According to national regulations and the Ethics Committee approval, no Data Monitoring Committee (DMC) will accompany this study.

### Statistical Analysis

#### Primary Outcome

A mixed model ANOVAs will be used to assess the clinical effects for primary outcome measure (MADRS), with intervention as between subject factor (active vs. sham tDCS), and time as within subject factor (weeks 2, 4, 8, 12, and 6 months). If there are significant baseline differences across the groups, those covariates will be included in the analysis (such as severity, anxiety, and quality of life). If significant main effects and/or interactions arise from the main analysis, *post-hoc* analysis corrected for multiple comparisons will be performed. If our hypothesis of prefrontal inter-hemispheric imbalance (as assessed by alpha power EEG) is confirmed, we will then conduct correlation analysis in order to assess whether these brain signatures correlate to long-term clinical effects in MDD.

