**Figure 2 F2:**
[figure not shown]
Schematic representation of the main phases of the trial. **(A)** Shows the timeline of assessments. **(B)** Details how interventions sessions will be administered by week.

This study will then be organized in 3 distinct phases. Phase 1: Recruitment and baseline assessments; Phase 2: Intervention; Phase 3: Post-treatment assessment and 6-month follow-up (Figure 1). Once eligibility is determined and consent provided, patients will be randomly assigned to one of the two groups in a 1:1 allocation ratio, by the means of a list generated by an automatic web-based randomization program.

After an initial baseline assessment (visit 1) (for more details see task 1), patients will receive 10 consecutive sessions (in two weeks) of active or sham tDCS (2 mA, 30 min), and 6 sessions of CBT every other day (3 CBT sessions per week). Patients may fail 1 or 2 sessions of tDCS and/or CBT; and in that case, they will have the opportunity to receive the missing session (s) in the following week. The primary outcome will be assessed by week 2, using MADRS. Other assessments will be also performed by week 2, such as EEG, and other clinical measures (see Table 1). By week 4 and 6, patients will receive additional booster sessions of the same intervention (active or sham tDCS followed by CBT). Patients will perform the same assessments on week 6 (Figures 2A,B). tDCS sessions will follow the same design previously tested by two members of our group, that showed significant clinical effects of tDCS alone, and tDCS combined with sertraline in moderate to severe MDD (21).

**Table 1 T1:** Summary and timeline of assessments.

	**Consent and Screening**	**Assessment pre-intervention**	**EEG pre-intervention**	**Interventions Session and tDCS**	**Assessment 15 days**	**EEG 15 days**	**Interventions Session and tDCS**	**Assessment post-intervention**	**EEG post-intervention**	**Follow-ups**	
				***Daily Sessions***			***Bi-weekly sessions***			***15 day, 1, 2, 3, and 5 months***	
	**Email / Visit 1**	**Visit 1**	**Visit 2**	**Visit 3-12**	**Visit 13**		**Visit 14-21**	**Visit 22**		**Visit 24 – 27**	
***Approximate visit time***	***1 h 30 min***	***30 min***	***1 h***	***50 min***	***30 min***		***50 min***	***30 min***		***30 min***	

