### Sample Size Calculation

For the sample size calculation, we assume an effect size(d) of 0.66 [upper limit for the 95% CI of the pooled effect size of tDCS on MDD (22) that for a two-side α of 0.05 and a power of 80%, requires a total of 76 patients (38 per group). We increased the sample size by 15% to 45 per group to account for unexpected factors. This sample size will be adequate to detect this magnitude of effect.

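### The primary analysis reads as a classical repeated-measures ANOVA over five visits to 6 months, which without imputation would exclude any patient missing one visit; a likelihood-based model should be named instead

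*Protocol article*

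**What the plan says.** Under Statistical Analysis, Primary Outcome, the article states: "A mixed model ANOVAs will be used to assess the clinical effects for primary outcome measure (MADRS"). The model is specified "with intervention as between subject factor (active vs. sham tDCS), and time as within subject factor (weeks 2, 4, 8, 12, and 6 months"). Post-hoc comparisons, corrected for multiplicity, follow if a main effect or interaction is significant. The paragraph mentions no random effects, covariance structure or likelihood estimation, and says nothing about missing MADRS values.

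The time point of the primary outcome is given elsewhere. The Abstract (Methods/Design) puts it at 6 weeks. The text after Figure 2, in the trial design section, puts it at week 2. The time factor contains week 2 but not week 6.

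Under Sample Size Calculation, "we assume an effect size(d) of 0.66", which "for a two-side α of 0.05 and a power of 80%, requires a total of 76 patients (38 per group"). Then: "We increased the sample size by 15% to 45 per group to account for unexpected factors". Under Randomization, allocation is 1:1.

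**The concern.** Pairing a between-subject arm factor with a within-subject time factor, then testing main effects and interactions with post-hoc comparisons, is the vocabulary of a split-plot ANOVA. In its standard form, that analysis needs one complete row of values per patient. A patient with MADRS at weeks 2, 4, 8 and 12 but not at 6 months contributes nothing unless the gap is imputed.

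The choice of visits makes this costly. Treatment lasts 6 weeks, so three of the five levels (weeks 8 and 12, and 6 months) fall after it ends. A missed late follow-up visit could therefore remove a patient whose value at week 2 or week 6, whichever is the primary time point, was observed. The primary comparison would then describe patients who completed follow-up, not the patients randomised, and it would waste data already collected.

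**Working it through.** **Inputs from the article.** Standardised effect d = 0.66, two-sided alpha 0.05, power 80%, 38 per group, raised by 15% to 45 per group, 1:1 allocation (Sample Size Calculation; Randomization). Five time levels (Statistical Analysis, Primary Outcome).

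**Inputs assumed.** The article gives no rate of missing assessments. The rates below are illustrative, and the same in both arms.

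**Step 1: the plan's own figures.** With a two-sample t-test (noncentral t) at d = 0.66, power is 0.7998 at 37 per group and 0.8104 at 38. So 38 is the smallest size that reaches 80%, as stated. For the increase, 38 / 0.85 = 44.7, rounded up to 45, as stated. (38 × 1.15 = 43.7 would give 44.) Both figures reproduce. Power at the full 45 per group is 0.87.

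**Step 2: complete patients if each visit is missed independently with probability m.** Complete per arm = 45 × (1 − m)^5.

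| m per visit | (1 − m)^5 | complete per arm, of 45 |
|---|---|---|
| 2% | 0.904 | 40.7 |
| 3% | 0.859 | 38.6 |
| 5% | 0.774 | 34.8 |
| 8% | 0.659 | 29.7 |
| 10% | 0.590 | 26.6 |

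**Step 3: complete patients if a share D drops out by 6 months and no other visits are missed.** Complete per arm = 45 × (1 − D): 10% leaves 40.5, 15% leaves 38.2, 20% leaves 36, 30% leaves 31.5.

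**Step 4: where the allowance runs out.** Set the complete number equal to 38.
- Per visit: m = 1 − (38/45)^(1/5) = 0.033, or about 3.3%.
- Total dropout: D = 1 − 38/45 = 0.156, or about 15.6%.

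**Step 5: data kept against data collected.** At m = 5%, the expected number of complete patients is 90 × 0.774 = 69.6 of 90, while 450 × 0.95 = 427.5 of 450 MADRS values are observed. A complete-row analysis loses about 23% of patients when 5% of values are missing. A likelihood-based model can use all the observed values.

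**Step 6: what this means for power.** The answer depends on which effect is tested.
- For a single-visit comparison at d = 0.66, power is 0.78 at 35 per arm and 0.66 at 27.
- For the effect averaged over five visits, assume a constant difference and a within-patient correlation of 0.6. The SD of the mean is then multiplied by sqrt((1 + 4 × 0.6)/5) = 0.825, so d becomes 0.66 / 0.825 = 0.80. Power is then 0.91 at 35 per arm and 0.82 at 27.

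Power therefore does not fall below 80% on every reading. The arm-by-time interaction was not evaluated.

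**The case against.** The strongest reply is that the article never says only complete patients are analysed. Its words include *mixed model*, which can mean a likelihood-based linear mixed model that uses every observed visit. Imputation is not excluded either. Rules for missing data and analysis populations are commonly left to an analysis plan or full protocol, and neither is shown. This stands as far as it goes: exclusion is inferred from the named method. It does not remove the point, because the article does fix a method and describes it in terms that fit the classical version better. If a likelihood-based model was meant, the wording should say so.

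Three stronger readings are tempting and are not supported.
- *That the trial would fall below 80% power.* The single-visit figures in Step 6 are illustrative. They do not carry over to a five-visit average, and all missingness rates are assumed. Under plain dropout of 15%, the planned 45 still leaves the required 38.
- *That the estimate would be biased in a known direction.* The size and direction of any bias depend on who drops out and why, and the article gives no basis for choosing a mechanism.
- *That the plan itself expects missed visits.* The sentence "Patients may fail 1 or 2 sessions of tDCS and/or CBT" concerns treatment sessions, which can be made up the following week. It says nothing about missed MADRS assessments.

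A fair caution about the remedy is that an unstructured covariance must be estimated from about 90 patients: 15 parameters for five visits (5 × 6 / 2) or 21 for six (6 × 7 / 2). That needs care but is not prohibitive.

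**Conclusion.** The point holds as a recommendation to change the named method. As described, the primary analysis reads as a classical repeated-measures ANOVA and, without imputation, would probably exclude any patient missing one of five visits, three of which come after treatment. At an assumed 5% or 10% missing per visit, independently, about 35 or 27 of 45 per arm would remain. The margin between 38 and 45 is used up at about 3.3% per visit or 15.6% total dropout. The loss of patients follows from the arithmetic once the classical reading and a missingness rate are granted. The article confirms neither, and nothing firmer can be said about power or bias. The change is worth making on either reading: it replaces a wasteful analysis if the ANOVA was meant, and it removes an ambiguity if a likelihood-based model was meant.

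**What to change.** Reword the primary analysis as a likelihood-based mixed model for repeated measures with arm, categorical time, arm-by-time interaction and unstructured covariance. Apply it to all randomised patients with any post-baseline MADRS, analysed as randomised.

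First reconcile the primary time point across the Abstract (6 weeks), the trial design section (week 2) and the analysis section (no week 6 level). Then include that visit in the model and name the between-arm contrast at that visit as the primary test. Without this step, a better model on the listed visits still could not estimate a week-6 effect. Keep an ANOVA on completers, if at all, as a sensitivity analysis.

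The cost is analysis wording. No patients or visits are added, because Table 1 already schedules MADRS at 15 days and after the intervention. The article reports the trial as still recruiting, so the change can be made before the data are analysed.

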## Abstract

**Background:** Major Depressive Disorder (MDD) affects more than 264 million people worldwide. Current treatments include the use of psychotherapy and/or drugs, however ~30% of patients either do not respond to these treatments, or do not tolerate the side effects associated to the use of pharmacological interventions. Thus, it is important to study non-pharmacological interventions targeting mechanisms not directly involved with the regulation of neurotransmitters. Several studies demonstrated that transcranial Direct Current Stimulation (tDCS) can be effective for symptoms relief in MDD. However, tDCS seems to have a better effect when used as an add-on treatment to other interventions.

**Methods/Design:** This is a study protocol for a parallel, randomized, triple-blind, sham-controlled clinical trial in which a total of 90 drug-naïve, first-episode MDD patients (45 per arm) will be randomized to one of two groups to receive a 6-weeks of CBT combined with either active or sham tDCS to the dorsolateral prefrontal cortex (DLPFC). The primary outcome will depressive symptoms improvement as assessed by the Montgomery-Asberg Depression Rating Scale (MADRS) at 6-weeks. The secondary aim is to test whether CBT combined with tDCS can engage the proposed mechanistic target of restoring the prefrontal imbalance and connectivity through the bilateral modulation of the DLPFC, as assessed by changes over resting-state and emotional task eliciting EEG.

**Discussion:** This study evaluates the synergetic clinical effects of CBT and tDCS in the first episode, drug-naïve, patients with MDD. First episode MDD patients provide an interesting opportunity, as their brains were not changed by the pharmacological treatments, by the time course, or by the recurrence of MDD episodes (and other comorbidities).

**Trial Registration:** This study is registered with the United States National Library of Medicine Clinical Trials Registry (NCT03548545). Registered June 7, 2018, clinicaltrials.gov/ct2/show/NCT03548545. Protocol Version 1.

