### Description of the Assessments

These instruments will be used at baseline, after the first 2 weeks of intervention, at the end of the 5-weeks of biweekly sessions and follow-up visits (up to 2 months after the intervention period) as detailed in the table below. Please see Table 1 for the complete assessments timetable.

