### Outcomes

#### Primary Outcome

For the depression assessment, we will use the Montgomery-Asberg Depression Scale (MADRS) as primary outcomes. Criteria for the use of this clinical scale will be the same as we previously used in Brunoni et al. (21). Secondary outcomes will include also the clinical response (categorical variable, defined as > 50% reduction of the baseline MADRS score), clinical remission (categorical variable, defined as a MADRS scores ≤ 10), and scores on the BDI.

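### The primary time point is week 6 in the Abstract and week 2 in the Methods, and the primary model cannot estimate the week-6 difference or change from baseline at any visit

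*Protocol article*

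**What the plan says.** **Primary time point.** The Abstract defines the primary outcome as improvement in depressive symptoms "as assessed by the Montgomery-Asberg Depression Rating Scale (MADRS) at 6-weeks". The Methods (Trial Design, Setting and Registration) state: "The primary outcome will be assessed by week 2, using MADRS". They add that the same assessments are repeated at week 6. The Outcomes section says only that "we will use the Montgomery-Asberg Depression Scale (MADRS) as primary outcomes", with no time.

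**Primary model.** Statistical Analysis, Primary Outcome, specifies a mixed-model ANOVA "with intervention as between subject factor (active vs. sham tDCS" and "time as within subject factor (weeks 2, 4, 8, 12, and 6 months". Baseline has one route in: "If there are significant baseline differences across the groups, those covariates will be included in the analysis (such as severity, anxiety, and quality of life". Post-hoc comparisons, corrected for multiplicity, follow if a main effect or interaction is significant. No single contrast is named as the primary test.

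**Schedule.** Table 1 places MADRS at baseline, at the 15-day assessment, post-intervention, and at follow-ups given as "15 day, 1, 2, 3, and 5 months". The text after Table 1 lists baseline, weeks 2, 4 and 6, and follow-ups up to 6 months. Description of the Assessments refers to five weeks of biweekly sessions and to "follow-up visits (up to 2 months after the intervention period".

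**The concern.** Week 2 and week 6 ask different questions. Week 2 comes after 10 of the 18 planned tDCS sessions (10/18 = 56%); week 6 is the end of the combined course. Calling each of them primary in a different place leaves the confirmatory hypothesis undefined.

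The model does not settle it. Followed literally, it leaves out the end-of-treatment visit named in the Abstract. With only post-baseline levels, its two treatment-related tests also do not measure improvement. The intervention main effect averages the arm difference over five visits. The interaction asks whether that difference varies among those visits, so a benefit that is constant from week 2 onward would give no interaction at all. Which of the two is the primary test is not stated.

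At stake is whether a positive or negative result can be tied to one hypothesis fixed in advance.

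**Working it through.** **1. The sample size, as a reference point.** Inputs from Sample Size Calculation: d = 0.66, two-sided α = 0.05, power 80%.
- Normal approximation: n = 2 × (1.960 + 0.842)² / 0.66² ≈ 36.0, so 37 per arm.
- Two-sample t-test: 37.02, so 38 per arm and 76 in total, as stated.
- Inflation: 38 / (1 − 0.15) = 44.7, so 45 per arm, as stated.

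The figure reproduces, with t-test power of 81.0% at 38 and 87.2% at 45 per arm. It describes one two-group comparison at one time. The analysis section names no such comparison.

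**2. What the listed model can estimate.** Take a cell-means model with arm by time, weeks counted from baseline, and 6 months taken as week 26. A contrast is estimable if adding it to the design matrix does not raise the rank.

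| Contrast, active minus sham | Estimable with the listed levels? |
|---|---|
| Score at week 2, 4, 8, 12 or 26 | Yes |
| Score at week 6 | No |
| Score at baseline | No |
| Change from baseline to week 2 | No |
| Change from baseline to week 6 | No |

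Adding baseline and week 6 as levels makes both week-6 contrasts estimable. A curve over continuous time could interpolate week 6, but the plan specifies time as a factor.

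**3. Do the listed levels match the visits?** Take a month as 30.4 days and, as an assumption, count Table 1 follow-ups from the end of week 6.

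| Table 1 follow-up | Weeks after treatment | Weeks from baseline |
|---|---|---|
| 15 days | 2.1 | 8.1 |
| 1 month | 4.3 | 10.3 |
| 2 months | 8.7 | 14.7 |
| 3 months | 13.0 | 19.0 |
| 5 months | 21.7 | 27.7 |

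- *Levels counted from baseline.* Week 2 matches the 15-day assessment, and week 8 matches the first follow-up. Six months is close to week 27.7. Week 12 falls between 10.3 and 14.7 and has no Table 1 visit. Week 4 is absent from Table 1 but is supported by the text that follows it.
- *Levels counted from end of treatment.* Weeks 2, 4, 8 and 12 lie close to 2.1, 4.3, 8.7 and 13.0. The model then holds follow-up only and contains neither candidate primary time point.

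Week 6 is missing on both readings.

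**4. Other schedule text.** The trial design places the twice-weekly booster sessions in weeks 3 to 6, which is four weeks. Description of the Assessments has five weeks of biweekly sessions and ends follow-up at 2 months. That conflicts with Table 1 and with the 6-month follow-up stated elsewhere.

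**5. Illustration only.** Suppose week 2 and week 6 were each tested at 5% and either could be claimed. Then P(at least one false positive) = 1 − P(|Z₁| < 1.96 and |Z₂| < 1.96), with (Z₁, Z₂) bivariate normal with correlation ρ.

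| ρ (assumed) | 0.3 | 0.5 | 0.7 | 0.9 |
|---|---|---|---|---|
| Probability | 9.5% | 9.1% | 8.3% | 7.0% |

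The document gives no correlation.

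**The case against.** The contradiction itself has no good answer. Several stronger inferences do, and a reader should not draw them.

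- **That no stated primary outcome can be estimated.** If weeks count from baseline, week 2 is a level. The between-arm difference in week-2 scores is then estimable, and under randomisation it is a valid comparison without baseline. The failure is complete only for the week-6 version.
- **That baseline is excluded outright.** Baseline severity may enter as a covariate. The weakness is that this depends on a significance test of baseline differences, so it is not a planned adjustment.
- **That week 4 is never assessed.** The text after Table 1 lists week 4 and also plans mood ratings at the end of each week. The conflict is between that text and Table 1.
- **That 5-month and 6-month follow-up contradict each other.** Five months after week 6 is week 27.7, about 6.4 months from baseline, so both may describe one visit. The 2-month limit is the clear conflict.
- **That the trial's type I error is about 9%.** No section plans to test both visits and claim either. The plan is an overall ANOVA with corrected post-hoc tests.

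It is also fair to say that follow-up visits in a repeated-measures model are not an error, provided the primary contrast is named. What remains is that none of these points puts week 6 into the model or decides between the two time points.

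**Conclusion.** The point stands in limited form. The primary time point is contradictory: week 6 in the Abstract, week 2 in the Methods, none in the Outcomes section. The primary model cannot estimate the week-6 between-arm difference and models change from baseline at no visit. These statements rest on the document's own list of levels, read as categories. The mismatch at week 12 also assumes that Table 1 follow-ups count from the end of week 6.

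The sample size is unaffected. The 7% to 9.5% range shows what leaving two candidate time points open could permit under assumed correlations; it does not measure the error of the analysis as planned. Because the defect concerns which hypothesis is confirmatory, it should be settled before unblinding.

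**What to change.** 1. State one primary time point in the Abstract, Trial Design, Outcomes and Statistical Analysis, for example week 6 as in the Abstract.
2. Include that visit as a level of the model. Use baseline MADRS as a pre-specified covariate, regardless of any test of baseline differences, or include it as a time level.
3. Name the between-arm contrast at that visit as the single primary test. Make the other visits, including follow-ups (and week 2, if week 6 is chosen), secondary.
4. State the origin from which weeks and months are counted. Then reconcile the visit times and follow-up length in Trial Design, Table 1 and the text after it, Description of the Assessments, and Statistical Analysis. The number of weeks of biweekly sessions must also be reconciled between sections.

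**Cost.** The trial is recruiting, so this is a substantive protocol and registry amendment, not an editorial correction, and it should be dated before unblinding. If week 6 is chosen, no new data are needed, because MADRS is already planned at baseline and week 6.
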